**Study Timeline:**

## Sample Size Calculation and Outcome (Primary and Secondary) Variable(s)

Study Arms:

1: Chlorine + Safe Storage

2: Safe Storage

3: Standard Practice

Hypothesis 1 (Main Hypothesis, Arm 1 vs. 3): Children who live in households that use tubewell water for drinking that is treated with effective chlorination and safely stored will have less diarrhea than households that use shallow tubewell water for drinking that is not treated and not safely stored.

Hypothesis 2 (Arm 1 vs. 2): Children who live in households that use tubewell water for drinking that is treated with effective chlorination and safely stored will have less diarrhea than households that use tubewell water for drinking that is safely stored but not treated with chlorine.

Hypothesis 3 (Arm 2 vs. 3): Children who live in households that use tubewell water for drinking that is safely stored but not treated will have less diarrhea than households that use tubewell water for drinking that is not treated and not safely stored.

While hypothesis 1 (the combined effect of chlorination and safe storage) is our main hypothesis, the study has been conservatively sized to have sufficient power to test hypothesis 2 (individual effect of chlorination), using the following assumptions:

- 2-day prevalence (as opposed to 7-day prevalence) used in calculations to be conservative
  - 14% longitudinal prevalence in Arm 3 (based on SHEWA-B data)
  - 11.6% longitudinal prevalence in Arm 2 (based on Roberts et al., 2001)
  - 9.1% longitudinal prevalence in Arm 1 (based on Arnold and Colford, 2007)
- 1 child between the ages of six months and two years per tubewell
- 5 follow-up visits per child
- 0.13 ICC and 1.50 design effect for repeated measures per child
- 10% drop-out
- One-tailed test with 95% confidence level

There is firm evidence from previous studies on the protective effect of household water treatment with chlorine, justifying a one-tailed test. Based on these assumptions, a sample size of 575 households per arm will have 80% power to detect the difference between Arms 1 and 2. Because of the many uncertainties in the sample size estimation, we will enroll 600 households in the Aquatabs and safe storage group, 600 households in the safe storage only group and 600 households in the standard habits and practices control group. This conservative sample size allows us to detect the difference between Arms 1 and 3 and test our main hypothesis with 99% power with either a one-tailed or a two-tailed test.

## Facilities Available

Describe the availability of physical facilities at site of conduction of the study. For clinical and laboratory-based studies, indicate the provision of hospital and other types of adequate patient care and laboratory support services. Identify the laboratory facilities and major equipment that will be required for the study. For field studies, describe the field area including its size, population, and means of communications.

ICDDR.B has maintained a field office in Fulbaria that will serve as the base station for field activities. Laboratory analyses will be carried out in the field office through the use of field kits designed for carrying out such tests in the absence of a fully-equipped laboratory.

The Fulbaria upazila has an area of 99,436 acres and a population of 396,000. The upazila consists of 13 unions, 104 mouzas (administrative units) and 135 villages. Fulbaria sadar union is about 22 kilometers from Mymensingh sadar and about 120 kilometers from Dhaka ICDDR,B center by road.

## Data Safety Monitoring Plan (DSMP)

All clinical investigations (biomedical and behavioural intervention research protocols) should include the Data and Safety Monitoring Plan (DSMP) to provide the overall framework for the research protocol’s data and safety monitoring. It is not necessary that the DSMP covers all possible aspects of each element. When designing an appropriate DSMP, the following should be kept in mind.

1. All investigations require monitoring;
2. The benefits of the investigation should outweigh the risks;
3. The monitoring plan should commensurate with risk; and
4. Monitoring should be with the size and complexity of the investigation.

Safety monitoring is defined as any process during clinical trials that involves the review of accumulated outcome data for groups of patients to determine if any treatment procedure practiced should be altered or not.

The interventions planned for this study, chlorine treatment of drinking water, and storage of water in a container that prevents re-contamination have been widely used and found safe. The dosage of chlorine will be controlled by the use of a single tablet for a known volume of water. Even if households made an error in dosing, the doubled or tripled the chlorine concentration would still not represent a substantial risk to human health. In addition, at such a high dosage effect on taste and smell of the water would make it unpalatable.

Although we do not expect any adverse outcomes, we will assess the well-being of household participants at each monthly visit. Field workers will refer members of households with serious health problems to appropriate care providers. They will record any serious health problems and we will track these regularly to see if there is any association with any of the interventions. In addition, participating subjects will be able to contact the local research investigator if they have any concerns.

## Data Analysis

Describe plans for data analysis. Indicate whether data will be analysed by the investigators themselves or by other professionals. Specify what statistical software packages will be used and if the study is blinded, when the code will be opened. For clinical trials, indicate if interim data analysis will be required to determine further course of the study.

The primary outcome will be longitudinal prevalence of diarrhea among children between the ages of six months and two years. If there are any children in a recruited household that are between the ages of two and five, their diarrhea outcome will be considered as well. We will use longitudinal prevalence because it is more strongly associated with malnutrition and mortality than is diarrhea incidence (Morris et al., 1996). We will collect diarrhea over 1 day, 2 day and 7 day recall periods. We will use a 7 day recall period to increase statistical power (Schmidt et al. 2010) if we confirm that the ratio of diarrhea cases in the past 24 hours (1 day recall) to cases that terminated between days 2-7 (the CT ratio) does not differ by randomized treatment group (Boerma et al. 1991). If the CT ratio differs by treatment group, it will indicate differential recall bias and so we will use a more conservative 2 day recall period in our primary analysis. Using STATA and/or SAS for data analysis, we will make the following three comparisons:

- Group 1 vs. 2: We will compare the longitudinal prevalence of diarrhea among children between the ages of six months and two years in households that receive chlorine water treatment and safe storage to households that receive safe storage. This will assess the contribution of water disinfection (separate from safe storage) to any reduction in diarrhea.
- Group 2 vs. 3: We will compare the longitudinal prevalence of diarrhea among children between the ages of six months and two years in households that receive safe storage only to households that receive no intervention. This will assess the effect of safe storage.
- Group 1 vs. 3: We will compare the longitudinal prevalence of diarrhea among children between the ages of six months and two years in households that receive chlorine water treatment and safe storage to households that receive no intervention. This will assess the combined effects of safe storage and disinfection.

We will assess the magnitude of the differences in longitudinal prevalence by group by calculating a risk ratio between the groups. We will evaluate if risk ratios differ from 1.0 at traditional testing levels (*P*=0.05) using robust standard errors that account for repeated observations within children (Zeger and Liang 1986). We will repeat the calculations using the longitudinal prevalence of diarrhea among children under the age of five as the outcome measure to allow us to compare our results to other findings from the literature that focus on children under five.

Secondary outcomes will include the proportion of households by group that have contaminated water as measured by H2S testing and by quantitative evaluation of total coliforms and *E. coli.* We will assess the proportion of samples within each group that have no evidence of contamination. We will compare whether these proportions are different than would be expected by chance using chi square when there are no repeated samples and using general estimated equations when repeated samples are analyzed from the same household.

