## Specific Aims:

Describe the specific aims of the proposed study. State the specific parameters, biological functions, rates, processes etc. that will be assessed by specific methods.

In a typical setting in rural Bangladesh where households use shallow tubewell water for drinking:

1. Evaluate the impact of chlorination and safe storage of drinking water on childhood diarrhea compared to standard water handling habits and practices during the dry as well as wet season.
2. Evaluate the impact of safe storage of drinking water on childhood diarrhea separate from chlorination of tubewell water during the dry as well as wet season.

##

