In contrast to interventions to improve water quality at the source, high quality intervention studies that improve water quality at the point of use through treatment of water in households show a 39% reduction in diarrhea (Fewtrell et al., 2005). Point of use water treatment typically produces water that is microbiologically less contaminated than water source improvements (Mintz et al., 2001). Moreover, storing water safely in the home by using storage containers with lids and spigots has been shown to result in improvements in health (Mintz et al., 1995, Roberts et al., 2001). The magnitude of the risk of diarrhea due to consumption of tubewell water in the rural Bangladesh setting is not defined, and so the relative importance of further water quality improvements through treatment and safe storage in households is unknown. An estimated 16,600 – 27,700 children die each year in Bangladesh from diarrheal disease (Tanaka et al., 2007). Since more than 90% of households in rural Bangladesh use tubewells as their source of drinking water (NIPORT, 2005), the question of the marginal benefit of further treatment for tubewell water is an important issue for child health in Bangladesh.

In the context of rural Bangladesh, seasons often affect tubewell water quality through rainfall patterns, with 9% of very shallow tubewells (<20 m) shown to be contaminated with E.coli during the dry season from November through April and 61% contaminated during the rainy season from May until the end of October (Leber et al. 2010). Seasonality also has an impact on water retrieval, storage and handling practices. Some shallow tubewells run dry during the winter months and families shift to alternative sources, such as irrigation pumps that draw water from deeper aquifers or deep tubewells that are located further away from the compound. Recent data from rural Fulbaria suggest that, over the course of the dry season, roughly 30% of respondents have stopped using the shallow tubewell that was their primary drinking water source at the onset of the dry season. It is therefore expected that the magnitude of the health risk from microbiological contamination of drinking water and consequently the effectiveness of water treatment and safe storage interventions will show seasonal variation.

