**Data Collection:** There will be one baseline visit and ten follow-up visits to participating households.

Baseline Visit: We will conduct a baseline survey including demographics, household description, socioeconomic status, pre-intervention water, sanitation and hygiene habits and baseline levels of diarrhea in children between the ages of six months and two years. If there are any children in a recruited household that are between the ages of two and five, we will collect diarrhea data on them as well to allow comparison of our results to other findings in the literature that focus on children under the age of five. During the baseline visit, we will assess the microbial quality of the tubewell and stored water for each study household using the hydrogen sulphide (H2S) test. Tubewell and stored water samples from a subset of 150 households (50 from each study arm) will be analyzed for total coliforms and E. coli using membrane filtration.

Follow-Up Visits: Every month a field research assistant will visit each participating household to conduct a follow-up survey and collect information on the prevalence of diarrhea among children between the ages of six months and five years in the 48 hours as well as seven days preceding the visit. We are using a 48-hour recall because this typically provides a more valid estimate than longer recall periods which lead to under-reporting of health outcomes (Alam et al., 1989, Ramakrishnan et al., 1999, Feikin et al., 2010). We are also using a seven-day recall because recent findings indicate that while this longer recall period leads to only minimal bias in terms of the accuracy of recall it can result in significant gains of statistical power (Arnold et al., 2011).We will visit households once every month, because more frequent visits provide little additional statistical power due to correlation of repeated measures on the same individuals (Schmidt et al., 2007).

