## Ethical Assurance for Protection of Human Rights

Describe the justifications for conducting this research in human participants. If the study needs observations on sick individuals, provide sufficient reasons for using them. Indicate how participants rights will be protected, and if there would be benefit or risk to each participants of the study.

This study enrols human subjects, because the study question addresses the issue of the impact of additional water treatment behavior on human health and the question can only be answered by enrolling human subjects. The objectives and study procedures will be explained to all candidate households and only households that provide informed consent will be enrolled. Households will be free to drop out of the study at any time.

Benefits to the study participants include that some participating families will receive water treatment and/or a water storage container. Moreover, if the study shows that treating tubewell water at the household level and storing it safely is effective in improving children’s health, the safe storage group and the non-intervention group will be given a six-month supply of chlorine tablets at the end of the study and the non-intervention group will also be given a safe storage container such that all study participants will ultimately have received water treatment tablets in addition to safe storage containers. At the end of providing free tablets, all three study groups will also be encouraged to continue to treat their water. If children are identified through the routine surveillance who appear seriously ill to do field research assistant, they will be referred to an appropriate healthcare facility.

If the participants consent to participate in the five additional follow-up and promotional visits, we will provide these intervention container and tablets to the control arm households after these additional visits. However, during reconsenting, we would provide all the participants color pencils/toys for their small kids. This would be a token of appreciation but not compensation, which will help for the intellectual development of their kids but has small monetary value.

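### Both aims ask for the effect in the dry and the wet season, but the listed comparisons give no season-specific estimate, and the power statement still describes five visits where ten are planned

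*Protocol*

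**What the plan says.** **Aims.** Specific Aims puts season into both aims. The first compares chlorination plus safe storage with usual practice: "compared to standard water handling habits and practices during the dry as well as wet season". The second isolates storage and names the same two seasons: "Evaluate the impact of safe storage of drinking water on childhood diarrhea separate from chlorination of tubewell water during the dry as well as wet".

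**Expectation.** The Background reports *E. coli* in 9% of very shallow tubewells in the dry season (November to April) and 61% in the rainy season (May to October). It concludes that "consequently the effectiveness of water treatment and safe storage interventions will show seasonal variation".

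**Follow-up.** Research Design and Methods gives a ten-month intervention and states: "There will be one baseline visit and ten follow-up visits to participating households". The Ethical Assurance section shows that half of these depend on a second consent: "If the participants consent to participate in the five additional follow-up and promotional visits".

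**Sizing.** The Sample Size section assumes "5 follow-up visits per child", an ICC of 0.13 and a design effect of 1.50. It arrives at 575 households per arm for 80% one-tailed power on Arm 1 versus Arm 2, and enrols 600 per arm.

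**Analysis.** Data Analysis says "Using STATA and/or SAS for data analysis, we will make the following three comparisons" and lists Groups 1 vs 2, 2 vs 3 and 1 vs 3. Each is summarised by a risk ratio tested against 1.0 with robust standard errors, and the calculation is repeated for children under five. Season is mentioned neither there nor in Hypotheses 1 to 3.

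**The concern.** The protocol names season in its aims and predicts that season changes the effect, but its listed comparisons contain nothing that estimates the effect by season. If they are followed literally, the result is one risk ratio averaged over two periods with very different source-water contamination. A benefit confined to one season would then appear as a modest year-round effect. Seasonal estimates added after the data have been seen would be post hoc, on a question the protocol itself raised beforehand.

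The visit count is a second, smaller mismatch. The power statement rests on five visits per child and the design has ten. A reader therefore cannot tell from the protocol what power the ten-visit analysis has, or what can be expected of a seasonal one.

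**Working it through.** **Inputs (Protocol, Sample Size section).** Prevalence 14% in Arm 3, 11.6% in Arm 2 and 9.1% in Arm 1; ICC 0.13; 10% drop-out; 5% level; 600 per arm. H1 is Arm 1 vs 3, H2 is Arm 1 vs 2 and H3 is Arm 2 vs 3.

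**1. The plan's own figure.** The two-proportion formula with pooled null variance and continuity correction, 11.6% vs 9.1%, one-sided 5%, 80% power, needs 1,914 observations per arm. Then 1,914 × 1.50 / 5 = 574.2, rounded up to 575. The match is exact with the listed drop-out left out; that omission is a separate matter. It confirms that the sizing uses five visits. So does the design effect: 1 + 4 × 0.13 = 1.52, close to the stated 1.50.

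**2. Effective observations per arm.** With 10% drop-out, 600 × 0.9 = 540 children remain.
- Ten visits: design effect 1 + 9 × 0.13 = 2.17; 540 × 10 / 2.17 = 2,488.
- Five visits: 540 × 5 / 1.52 = 1,776.

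**3. Power.** Power = Φ[(d − z·SE0) / SE1], where SE0 uses the pooled prevalence and SE1 the separate ones. For H2 over ten visits, d = 0.025, SE0 = √(0.1035 × 0.8965 × 2 / 2,488) = 0.00864 and SE1 = √((0.116 × 0.884 + 0.091 × 0.909) / 2,488) = 0.00863.
- One-sided: (0.025 − 1.645 × 0.00864) / 0.00863 = 1.25, power 89.5%.
- Two-sided, with 1.96: 0.94, power 82.5%.

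| One-sided / two-sided | Ten visits, both seasons together | Five visits, one season |
|---|---|---|
| H1 | >99.9% / >99.9% | 99.8% / 99.6% |
| H2 | 89.5% / 82.5% | 78.9% / 68.7% |
| H3 | 81.3% / 71.7% | 69.0% / 57.2% |

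The middle column assumes that every retained household re-consents. The right column assumes an even split of visits and the stated prevalences in each season.

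**4. Sensitivity for H2 (one-sided / two-sided).**
- Only 50% to 80% of households re-consent (assumed), ten-visit analysis: 85.0% / 76.4% to 87.8% / 80.3%.
- Four or six visits in a season: 74.0% / 62.9% or 82.3% / 73.0%.
- Control prevalence in a season of 7%, 10% or 18% (assumed) with unchanged risk ratios and five visits: 51.5% / 39.0%, 65.1% / 52.9% or 88.0% / 80.5%.

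**5. Seasonal contrast for H1.** Per season, SE(log RR) = √(0.86 / (1,776 × 0.14) + 0.909 / (1,776 × 0.091)) = 0.0953. The SE of the difference between seasons is 0.0953 × √(2(1 − r)).
- r = 0: SE 0.135; detectable ratio of risk ratios exp(−2.80 × 0.135) = 0.69.
- r = 0.13 / (1.52 / 5) = 0.43, the value implied by the stated ICC holding across seasons: SE 0.102; exp(−2.80 × 0.102) = 0.75.

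Both are for 80% power with a two-sided 5% test.

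**6. Illustration of averaging (assumed values).** With a risk ratio of 0.65 in the wet season, 1.0 in the dry, and equal prevalence and visits, the overall risk ratio is (0.65 + 1.0) / 2 = 0.825.

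**The case against.** **The text is silent on season; it does not exclude it.** This stands. A reader might infer that the protocol has decided against a seasonal analysis, but nothing says so. Season strata and interaction terms are often left to an SAP, which is not at hand. What remains is that the protocol does set out its comparisons and model, and that list does not deliver what its aims ask for.

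**The seasonal phrase in the aims might only mean that follow-up spans both seasons.** That reading is possible. The Background's prediction of seasonal variation in effectiveness makes the season-specific reading the more natural one, though not the only one.

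**Five visits is conservative.** Also correct. A reader might infer from the mismatch that the trial is underpowered. The arithmetic shows the reverse for the overall comparisons, since extra visits add power even with partial re-consent. Under an even split, the existing five-visit calculation is essentially the per-season calculation, and H1 stays above 99% there. The defect is that the documented power does not correspond to the planned ten visits.

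**Part of the seasonal shortfall is sidedness.** True. On the plan's one-tailed basis, per-season H2 has 78.9% power; 68.7% is the two-sided figure. The protocol never claims power for H3.

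**Re-consent losses.** A reader might want the 10% drop-out allowance to absorb households that decline the extra visits. The documents give no basis for this, because such a household still contributes its first five visits. Partial re-consent belongs in a sensitivity range.

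**Conclusion.** The point holds in a limited form and should be corrected. The listed comparisons contain no season-specific estimate or arm-by-season term, so followed as written they return one risk ratio averaged over both seasons, although both aims mention season and the Background predicts a seasonal difference. The five-visit sizing is outdated against a ten-visit design. It is conservative for the overall comparisons and leaves them valid.

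The main hypothesis can be examined by season without further enrolment: per-season power exceeds 99%, and the detectable seasonal ratio of risk ratios is about 0.69 to 0.75. Season-specific estimates for Arm 1 vs 2 and Arm 2 vs 3 will be less precise. These figures rest on an even split of visits, the stated prevalences applying in each season, and a between-season correlation of 0 to 0.43. None of these is given in the protocol, and the study timeline cannot be read in the available text.

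**What to change.** **Data Analysis.** For each of the three comparisons, pre-specify an arm-by-season term, with seasons defined by calendar date as in the Background (dry November to April, wet May to October). Report the dry-season risk ratio, the wet-season risk ratio and their ratio, with confidence intervals, beside the overall risk ratio.

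**Sample Size.** Replace the five-visit power statement with power at 600 per arm and 10% drop-out for ten visits (design effect 2.17) and for one season with five visits. Name the sidedness, and give a range for partial re-consent and for unequal numbers of visits per season. The table and ranges above can serve as a starting point.

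**Cost.** A few lines of analysis text and one power table, with no new data collection or enrolment. The downside is that season-specific estimates for Arm 1 vs 2 and Arm 2 vs 3 will be imprecise; they should be labelled so in advance.

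### The primary risk ratio is specified with no role for baseline diarrhea or age, a valid choice that gives up a modest amount of precision on the two secondary contrasts

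*Protocol*

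**What the plan says.** The Data Analysis section of the protocol names the effect measure, "We will assess the magnitude of the differences in longitudinal prevalence by group by calculating a risk ratio between the groups", and the test: "We will evaluate if risk ratios differ from 1.0 at traditional testing levels", at P=0.05, with robust standard errors that allow for repeated observations on the same child. It also sets the three pairwise contrasts and a rule for choosing between 7-day and 2-day recall. It gives no covariate any part in the comparison.

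Two candidate covariates are already available. Under Research Design and Methods (Data Collection, Baseline Visit), the baseline survey covers demographics and "baseline levels of diarrhea in children between the ages of six months and two years". Under Selection of Households, eligibility depends on a child aged six months to two years, so age has to be established at recruitment.

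The sample size section supplies the one figure that bears on how prognostic a child's own history is: "0.13 ICC and 1.50 design effect for repeated measures per child".

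**The concern.** A within-child correlation above zero means that a child's diarrhea status before the intervention carries information about the same child's status afterwards. A model that ignores it leaves that predictable part of the between-child variation in the error term. The trial bears the cost of measuring baseline diarrhea anyway, so any precision it offers is free.

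At stake is the power of the two contrasts that separate chlorination from safe storage, Arm 1 vs 2 and Arm 2 vs 3. The first of these sized the trial. With a log link, the adjusted arm coefficient is still a risk ratio, so the gain does not require a different effect measure.

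**Working it through.** **Inputs from the protocol.** Prevalence 9.1% (Arm 1), 11.6% (Arm 2) and 14% (Arm 3); ICC 0.13; design effect 1.50; five follow-up visits in the sizing; 10% drop-out; one-tailed 5% test; 575 households per arm for 80% power; 600 per arm enrolled. The Data Collection section plans ten follow-up visits, so both five and ten are shown.

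**The plan's own figure.** The pooled two-proportion formula for 11.6% vs 9.1% (one-sided 5%, 80% power) gives 1,835 observations per arm. 1,835 × 1.50 / 5 = 550.5, and 550.5 / 0.9 = 612 with drop-out. With continuity correction it gives 1,914, and 1,914 × 1.50 / 5 = 574.2, i.e. 575 before drop-out or 638 after it. So 575 is matched only when the listed drop-out is left out. The present point does not depend on this, and the calculations below use the 600 enrolled.

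**Step 1: variance of a child's follow-up mean.** With v visits and exchangeable correlation 0.13, relative to a single observation, it is V = (1 + (v − 1) × 0.13) / v.
- v = 5: 1.52 / 5 = 0.304
- v = 10: 2.17 / 10 = 0.217

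**Step 2: share explained by one baseline observation.** If the correlation between baseline and each follow-up visit is c, then R² = c² / V.
- c = 0.13, v = 5: 0.0169 / 0.304 = 0.056 (correlation 0.236)
- c = 0.13, v = 10: 0.0169 / 0.217 = 0.078 (correlation 0.279)

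**Step 3: households.** There are two equivalent ways to express this at 600 per arm. Households saved for the same precision are 600 × R², which gives 33 and 47. Extra households that an unadjusted analysis would need are 600 / (1 − R²) − 600, which gives 35 and 51. Together they span 33 to 51.

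**Step 4: sensitivity to decay.** The protocol gives no baseline-to-follow-up correlation. Setting it to 0.13 is an assumption, so lower values are shown, with 0.13 kept among the follow-up visits.

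| c | R², 5 visits | Saved | R², 10 visits | Saved |
|---|---|---|---|---|
| 0.13 | 0.056 | 33 | 0.078 | 47 |
| 0.10 | 0.033 | 20 | 0.046 | 28 |
| 0.065 | 0.014 | 8 | 0.019 | 12 |

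**Step 5: power.** The effective number of observations per arm is 600 × 0.9 / V, divided by (1 − R²) when adjusted. With c = 0.13:

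| Contrast | Visits | One-sided 5% | Two-sided 5% |
|---|---|---|---|
| Arm 1 vs 2 | 5 | 78.9% to 80.9% | 68.7% to 71.1% |
| Arm 1 vs 2 | 10 | 89.5% to 91.5% | 82.5% to 85.4% |
| Arm 2 vs 3 | 5 | 69.0% to 71.2% | 57.2% to 59.6% |
| Arm 2 vs 3 | 10 | 81.3% to 84.0% | 71.7% to 75.2% |

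Arm 1 vs 3 exceeds 99% in every case, before and after adjustment. Both sidedness columns are given because the sizing states "One-tailed test with 95% confidence level" while the analysis tests whether the ratio differs from 1.0. The gain ranges from 2.0 to 3.5 points. At c = 0.10 it is about 1 to 2 points, and at 0.065 it is under 1.

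The R² argument is a linear-model approximation applied to a log-link model for a binary outcome. Age would add something, but the protocol gives nothing from which to size it, so it is not counted.

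**The case against.** The strongest objection is that the protocol never says the analysis is unadjusted. It is silent on covariates, and the covariate set is often left to a statistical analysis plan, which may exist and is not at hand. This stands as a limit on the claim: a reader might infer that the protocol has fixed a crude analysis, and the text does not go that far. What remains is that the section chooses its effect measure, variance method, contrasts and recall rule, and gives covariates no role.

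Second, a crude risk ratio with robust errors is valid in a block-randomized trial of 600 per arm. A reader might infer that chance imbalance in baseline diarrhea is left as an uncorrected bias. It is not: the standard error already allows for it. This objection stands in full.

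Third, a reader might infer that the chlorination contrast, Arm 1 vs 2, is generally short of power and needs rescue. The protocol's figures do not support that. With the ten planned visits it has 82.5% (two-sided) to 89.5% (one-sided) without adjustment. It falls below 80% only with five visits, and of the two contrasts only Arm 2 vs 3 tested two-sided stays below 80% with ten.

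Fourth, the size is conditional. The Background section expects the risk to vary by season, and the children age over ten months, so a constant 0.13 is optimistic. The sizing is built on 2-day prevalence, whereas the primary analysis may use 7-day recall, for which no ICC is given. This also stands, and it is why a range is reported.

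**Conclusion.** The point holds as a modest, free improvement in efficiency. Nothing in the planned analysis is invalid or biased. If the ICC of 0.13 carries over from baseline to all follow-up visits, adjusting for baseline diarrhea is worth about 33 to 51 households per arm, or 2 to 3.5 power points on the two contrasts that separate chlorination from storage. With a correlation of 0.065 to 0.10 it is worth about 8 to 28 households. The main hypothesis gains essentially nothing. These figures rest on exchangeable correlation among follow-up visits, 10% loss, the protocol's 2-day prevalences and a linear approximation. The contribution of age is left unquantified.

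**What to change.** In the Data Analysis section, define the primary model as a log-link (modified Poisson) regression of diarrhea on arm. Adjust it for the child's baseline diarrhea, measured over the same recall window as the outcome, and for age at enrolment, with robust errors clustered on the child or household. Fix the covariates before any unblinded analysis, and report the crude risk ratio alongside. Calendar month need not be a required covariate; nothing in the protocol's figures supports a gain from it.

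The cost is a few lines of protocol or SAP text. The protocol does not state the recall window of the baseline diarrhea question, so confirm that the baseline questionnaire covers the 2-day and 7-day windows. If a SAP already names these covariates, a cross-reference to it is enough.
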